### Study aims

The primary objective of this study is to determine the effect of a multi-faceted community-based salt reduction intervention on mean salt intake, as estimated from measures of 24-hr urinary sodium excretion made before and after the intervention is implemented. The null hypothesis to be tested is that there will be no change in sodium excretion.

The secondary objectives are to determine the effects of the salt reduction intervention, by comparing measures before and after the intervention, on (1) population knowledge, attitudes and behaviour toward salt intake and (2) the sources of sodium in the diet, as estimated from 24-hr dietary recalls.

Exploratory objectives will be to examine (1) social inclusion as a determinant of response to the intervention; (2) the potential for a volunteer sample to provide estimates of population salt consumption and changes in population salt consumption; (3) whether spot urine samples can provide estimates of population salt consumption and changes in population salt consumption and (4) the association between urinary iodine excretion and urinary sodium excretion in females aged 20–45 years.

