*A single 24-hr urine collection* will be obtained with the first voided urine upon waking on the day of collection being discarded and participants then collecting all voided urine up to and including the first void the following morning. The times at the beginning and the end of urine collection are recorded. During the morning of the collection period a *single morning spot urine sample* will be obtained by asking participants to collect a sample into a 30 ml container. The volumes of the spot sample and the remainder of the 24 hr urine will be recorded and each will be separately assessed for sodium, potassium, creatinine and iodine. The volume and concentration data for each sample will be combined to derive the 24-hr sodium excretion estimate for each individual. The urinary sodium concentration will be measured by ion-selective electrode with the buffered kinetic Jaffe reaction without deproteinisation used for assay of urine creatinine (Cobas Integra 400). The urinary iodine measurement will be completed by using ammonium persulfate digestion prior to Sandell-Koltoff reaction in a microtitre plate format. Suspected inaccurate urine collections (i.e. urinary creatinine < 4.0 mmol/day for women, or < 6.0 mmol/day for men, or a 24-hr urine collection of < 500 ml for either sex) and extreme outliers for urinary creatinine (> 3 standard deviations from the mean) will be excluded from the primary analysis.

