### Data analysis

The characteristics of the full baseline and follow up samples will be summarised and compared, as will the characteristics of the volunteers, those selected at random and those for which paired baseline and follow-up specimens are available.

For each individual, the 24-hr sodium excretion value (mmol/day) will be calculated as the concentration of sodium in the spot urine (mmol/L), multiplied by the spot urine volume (L/day) added to the concentration of sodium in the remaining urine (mmol/L) multiplied by the volume of the remaining urine (L/day). The conversion from mmol to grams will be made by dividing by 17 and the conversion from sodium (Na) to salt (NaCl) by multiplying by 2.542.

The primary comparison between baseline and follow-up levels of 24-hr urinary sodium excretion will be made using an inverse-variance weighted fixed effect pooled estimate of the effects in the sub-sets of participants. The primary analysis will be supplemented by subsidiary analyses that separately explore the baseline and follow-up differences for 1) the volunteer sample, 2) the random sample and 3) the sample for which both baseline and follow-up specimens are available. Differences will be tested using t-tests and paired t-tests. The analysis will be unadjusted unless there is evidence that the baseline and follow-up samples differ in regard to age, sex or body mass index, in which case these covariates will be included in the models.

Bland-Altman plots will be used to explore the agreement between spot urine and 24-hr urine collections, and to determine whether the agreement between the two methods of collection varies across different levels of sodium excretion.

Daily iodine intake will be estimated by multiplying the concentration of iodine in the urine measured in μg/l by 0.0235 and by body weight measured in kilograms [20]. Urinary iodine status data will be summarised as median urinary iodine excretion values and the proportions with iodine deficiency and iodine sufficiency according to the World Health Organization and the International Committee on the Control of Iodine Deficiency Disorders (ICCIDD) [21]. Mann–Whitney U tests will be used to compare differences in urinary iodine excretion according to World Health Organization urinary salt excretion target of ≥ 5 g/day and < 5 g/day, while general linear models will be used to investigate the continuous association between iodine and sodium excretion.

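### Daily iodine intake is estimated with a body-weight formula that assumes urine volume, although volume and iodine are both measured in the same 24-hr collection

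*Protocol article*

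**What the plan says.** The Data analysis section of the protocol article obtains daily iodine intake by multiplying urinary iodine concentration "by 0.0235 and by body weight measured in kilograms", with a citation but no derivation of the constant. It does not say whether the concentration comes from the spot sample, the remainder or both.

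The Data collection section describes "A single 24-hr urine collection" per participant, from which a morning spot sample is taken. Volume is noted for both parts, and "each will be separately assessed for sodium, potassium, creatinine and iodine". For sodium, "The volume and concentration data for each sample will be combined to derive the 24-hr sodium excretion estimate for each individual". The Data analysis section writes this out as spot concentration × spot volume plus remaining concentration × remaining volume. No matching calculation is given for iodine.

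The iodine objective, under Study aims, is the last of four exploratory objectives: "the association between urinary iodine excretion and urinary sodium excretion in females aged" 20–45 years. The medians, the Mann–Whitney comparison and the linear models in the Data analysis section are all worded on iodine excretion. The 0.0235 formula is attached only to intake.

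**The concern.** A concentration in µg/L becomes µg/day only when multiplied by litres per day. The formula contains no recorded volume, so 0.0235 × weight must do that work, together with any recovery allowance inside the constant. Such a substitute is reasonable when volume is unknown. Here it is known for the same person on the same day.

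Two consequences follow for the intake estimate:

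- Each person's value is wrong in proportion to the gap between assumed and actual volume.
- Body weight enters the value directly, whether or not iodine intake is related to weight.

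The second would matter most if the formula value were ever set against sodium excretion. Sodium may itself rise with body size, and a shared dependence on weight would then look like an iodine–sodium link.

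**Working it through.** **Inputs from the protocol article.** The constant 0.0235 and the use of weight (Data analysis); recorded volumes and iodine assays for both parts of the collection (Data collection); the lower volume limit, "a 24-hr urine collection of < 500 ml for either sex" (Data collection). The article gives no derivation of 0.0235, so there is no figure of the plan's own to reproduce.

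**Inputs assumed.** Volumes above 0.5 L, the body weights, 90% urinary recovery, and the simulation distributions below.

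**Formula against measurement.** Let V be total volume, W weight, and C the volume-weighted concentration of the whole collection.

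- Measured excretion = C_spot × V_spot + C_rest × V_rest = C × V.
- Formula value = C × 0.0235 × W.
- Ratio to measured excretion = 0.0235 × W / V.
- Ratio to intake, if 90% is excreted = 0.9 × 0.0235 × W / V.

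If only the spot concentration is used, both ratios are further multiplied by C_spot / C.

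**At 70 kg:** 0.0235 × 70 = 1.645 L/day, and 0.9 × 1.645 = 1.4805.

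| V (L/day) | Ratio to excretion, 1.645/V | Ratio to intake, 1.4805/V |
|---|---|---|
| 0.5 | 3.29 | 2.96 |
| 1.0 | 1.65 | 1.48 |
| 1.5 | 1.10 | 0.99 |
| 2.0 | 0.82 | 0.74 |
| 3.0 | 0.55 | 0.49 |

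**Dependence on weight.** The assumed volume is 0.0235 × 50 = 1.175 L at 50 kg and 0.0235 × 100 = 2.35 L at 100 kg. At equal concentration the heavier person is assigned twice the intake.

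**Simulation under assumptions not in the document.** Weight had mean 78 kg and SD 16. Volume was lognormal with mean 1.7 L and CV 30–50%, with values under 0.5 L excluded. True iodine excretion had CV 30–50% and was independent of weight.

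- Formula/measured ratio, central 95% range: 0.53–2.20 at volume CV 30%, widening to 0.42–3.03 at CV 50%.
- Rank correlation of the formula value with true excretion: 0.48–0.78.
- Rank correlation of the formula value with weight: 0.29–0.43, where the truth is 0. If volume itself correlates 0.3 with weight, this falls to 0.11–0.28.
- If sodium correlates 0.4 with weight and iodine is truly unrelated to sodium, the formula value has a rank correlation of 0.12–0.17 with sodium. Measured excretion shows about 0. This result applies only if the formula value is used in the sodium analysis, and the simulation includes no collection error.

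**Collection error under the alternative.** On the log scale, suppose sodium and iodine are unrelated with SD 0.4 each, and share a completeness error of SD s. The induced correlation is s² / (0.16 + s²). With s = 0.10 it is 0.01/0.17 = 0.06; with s = 0.20 it is 0.04/0.20 = 0.20.

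**The case against.** **The tests are not stated on intake.** A reader might infer that the planned iodine–sodium association is already contaminated by body weight. The document does not support that. The objective, the Mann–Whitney test and the linear models all name excretion, and nothing says the formula value enters them. How iodine excretion is computed is not spelled out, but an article may leave that to a fuller document. This objection stands, and the spurious-association result is only conditional.

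**The reach is small.** No listed objective concerns iodine intake itself. The formula yields a descriptive estimate beneath one exploratory objective restricted to younger women. This stands too. It limits the importance of the point without making the formula a good choice.

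**The ratios can mislead.** The formula targets intake, so dividing it by excretion compares unlike quantities, and 3.29 sits exactly at the exclusion limit. Near 1.5 L the formula agrees well with measurement. This is fair, and is why the table includes 1.5 L and a recovery-adjusted column. The adjustment lowers every ratio by the same 10% and leaves the spread across volumes intact. Likewise, the comparison of 50 kg with 100 kg overstates bias to the extent that volume rises with weight.

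**Measured totals have a weakness of their own.** Over- or under-collection scales sodium and iodine together, which can create a positive correlation of a size comparable to the one the formula could produce. This stands, and the remedy must deal with it.

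**Conclusion.** The point holds for estimated intake. The plan fixes a formula that replaces a measured volume with an assumed one, when everything needed for direct calculation is collected and already used that way for sodium. For a 70 kg participant the estimate runs from about three times the measured value at the lowest accepted volume to about half at 3 L/day, with or without an assumed 90% recovery, and it is close to right near 1.5 L. Those volumes above 0.5 L, the recovery figure and the simulation distributions are assumptions. The dependence on weight at a given concentration is not an assumption, since it is part of the formula.

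The primary sodium endpoint and the secondary objectives are untouched. The claim does not extend to saying that the planned iodine–sodium analysis is biased; that would follow only if the formula value were used there. The change is worth making because it is cheap.

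**What to change.** 1. Define 24-hr iodine excretion (µg/day) as spot concentration × spot volume + remaining concentration × remaining volume, and state that this is the variable used in the sodium association.
2. If intake is to be reported, derive it from that total with an explicitly stated recovery fraction. The article gives none, so the sponsor must supply and justify it.
3. Keep the 0.0235 formula only as a comparison method: apply it to the spot concentration and set it against the value based on measured 24-hr excretion.
4. State that the volume and creatinine exclusions, now written for the primary analysis, also apply to the iodine analysis. Add a sensitivity analysis for collection error, for example one adjusted for creatinine, which is assayed in both parts of the collection.

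No new data are needed. The cost is one changed formula, one stated recovery fraction and one sensitivity analysis. The remaining drawback is that the exclusions reduce, but do not remove, the error that sodium and iodine share through a common collected volume, so a weak positive association should be read with that in mind.

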### Ethics and dissemination

Permission to undertake the study was obtained from the Lithgow City Council and the project was approved by the University of Sydney Human Research Ethics Committee. Written consent was obtained from all participantswho were free to discontinue their participation at any time, with no explanation required. The findings of this research will be disseminated through conference presentations, peer-reviewed publications and the general media.

### Project status

The baseline community assessment was undertaken in the first and second quarters of 2011 and the follow-up assessment will be done in the first and second quarters of 2014. The intervention will be implemented from the third quarter of 2013 to the second quarter of 2014. The findings of the baseline assessment were used to inform the design of the community-based salt reduction intervention.

## Discussion

This study will provide a robust evaluation of the effectiveness of a community-based intervention seeking to reduce dietary salt intake using the Communication for Behavioural Impact framework. The results will provide important new evidence to inform the design and implementation of current and future salt reduction policies in Australia. The results will also have important international implications because following the recent WHO recommendations for the control of non-communicable diseases [9], many countries are now seeking to achieve a reduction in average population salt consumption [22,23].

In addition to making an estimate of the effectiveness of the salt reduction intervention itself, the study also seeks to address important practical issues in the research field. In particular, to quantitatively address the question of whether the accepted best method for assessing population salt intake, the collection of 24-hr urine specimens from a random sample, might be substituted with other more practical approaches [24,25]. Response rates in surveys requiring 24-hr urine collection are generally low because of the significant participant burden involved with sample collection [26-28]. This study will determine the impact of substituting 24-hr urine samples with spot urine samples and of using a volunteer rather than a randomly selected population sample. While both approaches are somewhat non-intuitive, there are now some data suggesting that in selected circumstances these methods may provide valid estimates of average population salt consumption levels and changes in salt consumption over time [29,30]. Identifying simpler, lower cost approaches to developing and monitoring salt reduction programs has been identified as a priority by the World Health Organization in its efforts to achieve more widespread uptake of national salt reduction programs [31]. The capacity to use a spot urine collection to estimate 24-hr sodium excretion has been a particular focus of recent research efforts and appears to show considerable promise [32-35] although there is need for further validation of the procedures and equations used [36].

In parallel to the global roll out of salt reduction efforts there is a need to ensure that actions to control the impact of iodine deficiency are not adversely impacted [37]. Iodisation of salt is the preferred method for iodine deficiency disorder elimination [38] and there is a theoretical risk that a highly effective salt reduction program could reduce the effectiveness of this strategy. Accordingly, it is proposed that teams working on salt reduction engage closely with those involved with the elimination of iodine deficiency disorder to coordinate efforts. Specifically, a World Health Organization consultation held last year [39], highlighted the inadequacy of current estimates of iodine consumption for many countries, including Australia, and identified the potential for joint analysis of urine samples from population surveys to address this issue. The meeting also emphasised that the objectives of both iodine deficiency elimination programs and salt reduction programs can be achieved through the collaborative implementation of policies and careful monitoring of salt and iodine levels. Specifically, it was recommended that if salt reduction efforts are so effective as to decrease iodine consumption from salt, then the levels of iodisation in salt should be increased [39]. This study will be one of the first opportunities since that meeting to implement the proposed joint approach and explore whether urinary iodine excretion varies according to World Health Organization urinary salt excretion targets and the estimated proportion of sodium derived from fortified sources of salt.

The primary evaluation done within this study benefits from before and after assessments of salt consumption based upon the preferred method of 24-hr urine collection, with the use of standard checks for completeness of the specimens based upon volume and urine creatinine excretion. The sample size is only moderate but the study, nonetheless, has the power required to detect plausible changes in salt consumption. The location of the study in a single town in a regional area of New South Wales will compromise the direct generalizability of the study findings to Australia as a whole although there are likely to be elements of the findings that are viewed as applicable to a range of other settings. The inclusion of alternate methods of estimating salt consumption and the relationship between salt and iodine consumption will provide important new evidence on the feasibility and strength of these approaches and will inform national and global guidelines in this field.
